**LIST OF FIGURES**

[Figure 1: Study Schematic 34](#_Toc503183717)

LIST OF ABBREVIATIONS

| AE | adverse event |
| --- | --- |
| AIx | Augmentation Index |
| BAT | British American Tobacco (Investments) Ltd. |
| BMI | body mass index |
| BoBE | biomarker of biological effect |
| BoE | biomarker of exposure |
| CO | carbon monoxide |
| CPD | cigarettes per day |
| CRU | Clinical Research Unit |
| CTA | Clinical Trial Authorisation |
| CYP | cytochrome P450 |
| EC | ethics committee |
| ECG | electrocardiogram |
| eCRF | electronic Case Report Form |
| FDA | Food and Drug Administration |
| FEV_1_ | forced expiratory volume in 1 second |
| FTCD | Fagerström test for cigarette dependence |
| FVC | forced vital capacity |
| IB | Investigator’s Brochure |
| ICF | Informed Consent Form |
| ICH | International Council for Harmonisation |
| ITT | intent-to-treat population |
| LED | light-emitting diode |
| MHRA | Medicines and Healthcare products Regulatory Agency |
| MRTP | modified risk tobacco product |
| NGP | Next Generation Product |
| NO | nitric oxide |
| NRT | nicotine replacement therapy |
| OTC | over-the-counter |
| PP | per-protocol population |
| QTcF | QT interval corrected for heart rate using Fridericia’s method |
| SAE | serious adverse event |
| THP | tobacco heating product |
| VAS | visual analog scale |
| WBC | white blood cell |
| WHO | World Health Organisation |

DEFINITION OF TERMS

| Baseline assessments | Assessments that occur before the product test on Day 1 |
| --- | --- |
| Concomitant medication | Concomitant medication refers to all medication taken during the study conduct period from the Informed Consent Form (ICF) signature onwards. Medications started prior to signing of the ICF but which the subject continued to take during the study, were considered to be concomitant medications. |
| Conventional cigarette | Conventional cigarette refers to commercially available manufactured cigarettes, and excludes other tobacco products including hand-rolled cigarettes, cigars, pipes and bidis. |
| Enrolled not randomised | Any subject in Arms A or B who is enrolled onto the study on Day 1 but who withdraws or is withdrawn prior to randomisation. |
| Exposure period | From start of randomised product use (Arms A or B) on Day 1 until Check‑out from the clinic on Day 360. |
| Follow-up | Follow-up Visit will occur within 28 days following Check-out on Day 360. |

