- Blood sampling for primary endpoint biomarkers, BoE, BoBE, and exploratory endpoints
- Nasal transcriptomics sampling
- Carbon monoxide and NO breath tests
- Physiological endpoint assessments (body weight/waist circumference, carotid/femoral pulse wave velocity, 6-minute walking test, finger plethysmography)
- Questionnaire administration
  - 1. Continue-to-Smoke/Next Generation Product Population Only

Following safety assessments but prior to randomisation, product use training and demonstration will occur for subjects in the continue-to-smoke/THP population. Subjects will be offered the opportunity to trial up to 2 THP sticks. Product use will be separated by a minimum of 15 minutes during which subjects will not be allowed to use any nicotine‑containing products. The purpose of the product test is to allow subjects to experience the THP that they could be randomised to. If subjects decide that they do not wish to continue in the study following the product test, they will be withdrawn prior to randomisation. Subjects will be informed that there is an approximate 24.5% chance of being asked to continue to smoke their own brand cigarettes, and a 75.5% chance of being asked to smoke the THP.

Following the product test, subjects willing to take part in the trial will be randomised as described in Section 4.4. An additional, more detailed product use training and demonstration may be performed after randomisation, which may include, but may not be limited to, a demonstration of cleaning and storage instructions.

Prior to Check-out on Day 1, subjects randomised to Arm B will be provided with the investigational product.

Following randomisation, subjects will be instructed to use only their assigned product. As non-compliance with the study products may occur, there will be a 14 day transition period following Visit 1 where non-compliance is tolerated. After this period, subject non‑compliance will be assessed on an individual basis, and may lead to subject withdrawal as described in Section 3.3.

- - 1. Intend-to-quit Population

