**Mild** Easily tolerated; does not interfere with normal daily activities; does not require intervention

**Moderate** Causes some interference with daily activities; minimal, local or non‑invasive intervention indicated

**Severe** Medically significant event; daily activities limited or completely halted; hospitalisation or prolongation of hospitalisation indicated

Every reasonable effort will be made to follow-up subjects who have an AE at Follow-up, if possible, until resolution.

Any AE assessed as related to the study product will be assessed for its expectedness. An AE will be regarded as ‘unexpected’ if its nature or severity is not consistent with information already known about the study product, and is not listed in the current Investigator’s Brochure (IB).^19^ The IB provides further detail on signs or symptoms that might be expected with the use of the study product, including information relating to malfunction or misuse.

- 1. SAE Reporting

All AEs occurring during this clinical study will be recorded from time of the subject signing the ICF until the end of the study. The Investigator or their appropriately qualified designee will review each event, grade its severity and assess its relationship to the product consumption and/or the study procedures. The date of onset, time of onset, and outcome of each event will be noted.

If any of the above AEs are serious, special procedures will be followed. The Investigator will report all SAEs to the Covance Pharmacovigilance and Drug Safety Services Department within 24 hours. This information must be sent by fax by filling out the serious AE form. Written reports must then be submitted within 48 hours, whether or not the serious events are deemed related to study procedures or products. The EC will be notified by these reports.

If an SAE occurs during this study, the Medical Monitor will be contacted.

- - 1. Abnormal Results of Laboratory Tests

Any clinical safety laboratory results that are outside of the normal reference range will be reviewed for clinical significance by the Investigator or their appropriately qualified designee. If the abnormal result is considered to be of clinical significance, it will be recorded as a concomitant disease (prior to enrolment) or an AE (after enrolment). As for other AEs, the relationship to the study product, intensity, seriousness and outcome of abnormal clinical safety laboratory results will be recorded.

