1. DATA ANALYSIS
   1. General Considerations

Covance will perform the data analysis. The results of the study will be reported in a clinical study report. A detailed Statistical Analysis Plan describing the methodology to be used will be issued to the Sponsor for review and finalised prior to database lock.

In general, continuous variables will be presented by means of descriptive statistics (n, mean, standard deviation, median, minimum and maximum) and categorical variables will be displayed by means of frequency tables and, where appropriate, shift tables. All summaries will be presented by study arm, sex, age, and timepoint.

All data collected for the study will be presented as data listings for each subject.

- 1. Analysis Populations

The statistical analysis will be based on separate, hierarchically organised analysis populations defined as the following:

**Safety population** - All subjects who smoked at least one cigarette or had at least 1 safety assessment on Day 1.

**Intent-to-treat population (ITT)** - All subjects who were assigned and had at least 1 valid assessment of a biomarker variable.

**Per-protocol population (PP)** - All subjects who had a valid assessment of a biomarker variable and completed study according to the protocol (no major protocol deviations).

All listings will be based on the safety population. The baseline and demographics data will be summarised on all 3 populations. The safety data will be summarised based on the safety population only and the remaining data will be summarised for both the ITT and PP populations.

If there is less than a 10% difference between the ITT and PP populations then the summaries will only be based on the PP population.

- 1. Statistical Analysis of Primary and Secondary Objectives

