Product use compliance is a critical part of this study, as failure to fully replace cigarettes with the THP product would reduce or cancel the expected biomarker changes that would be observed if the product is used as indicated. To aid compliance assessment we will use a haemoglobin adduct of acrylonitrile, CEVal. Acrylonitrile is below the detection limit in the THP product emissions but can be found in cigarette smoke. We will use different thresholds for CEVal in ancillary analyses to deduce product use compliance. These thresholds have been calculated based on a previous study where this biomarker was reported for a modified combustible prototype cigarette.

The interim analysis on Day 90 will be performed on a subset of subjects who were enrolled on to the study on or before the day that the 42^nd^ subject was enrolled on to Arm A, and were still enrolled on the study at Day 90. This was chosen to ensure that 30 subjects on Arm A were still enrolled on the study at Day 90 to give sufficient power to detect the statistical difference between the two arms for Total NNAL.

- 1. Safety Data Summary and Analysis

All safety data will be summarised for all safety parameters based on the safety population, stratified by study arm.

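### Adverse events from the pre-randomisation THP product test are tabulated by the arm assigned afterwards: under cigarettes for later Arm A subjects, and in no by-arm summary for subjects withdrawn after the test.

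*Protocol*

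**What the plan says.** The relevant rules are all in the Protocol.

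- **Product test (Section 6.2.1).** Its timing is fixed: "Following safety assessments but prior to randomisation, product use training and demonstration will occur". Then: "Subjects will be offered the opportunity to trial up to 2 THP sticks". Of subjects who decide after the test not to go on, it says that "they will be withdrawn prior to randomisation".
- **Name for these subjects (Definition of Terms).** The category enrolled not randomised covers a subject "who is enrolled onto the study on Day 1 but who withdraws or is withdrawn prior to randomisation".
- **Collection of events (Section 8.4).** "All AEs occurring during this clinical study will be recorded from time of the subject signing the ICF until the end of the study". Section 8.2 adds onset time and the investigator's view of the relationship to product use.
- **Safety population (Section 9.2).** "All subjects who smoked at least one cigarette or had at least 1 safety assessment on Day 1".
- **Tabulation (Section 9.4).** "All safety data will be summarised for all safety parameters based on the safety population, stratified by study arm".
- **Arms (Section 3.1.2).** Membership of Arm A or B comes from randomisation, and membership of Arm D or E from assignment.
- **Exposure period (Definition of Terms).** It runs "From start of randomised product use (Arms A or B) on Day 1" and so leaves out the product test.

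**The concern.** The product test is real exposure to the investigational product, yet it takes place before the subject has an arm. Tabulating its adverse events by the arm assigned later attaches some THP reactions to conventional cigarettes. It also leaves others with no column at all.

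Monitoring the safety profile of THP users and cigarette smokers is a stated secondary objective. The subjects without a column may also be the most informative ones, because a bad reaction to the test stick is a plausible reason to decline. The protocol plans no count of those who declined or of their events.

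**Working it through.** **1. Where each test reaction goes under the stated rules**

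| Subject after the test | In safety population (9.2)? | Study arm (3.1.2) | Column under 9.4 |
| --- | --- | --- | --- |
| Withdrawn before randomisation | Yes: the Visit 1 safety assessments precede the test | None | None |
| Randomised to Arm A | Yes | A | Conventional cigarettes |
| Randomised to Arm B | Yes | B | THP |

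The exposure-period definition does not change the third row, because neither Section 9.2 nor Section 9.4 restricts the safety summaries to that period.

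**2. Share of randomised subjects in each arm**

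Inputs: 65 planned for Arm A and 200 for Arm B (Section 3.1).

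- Arm A: 65 / (65 + 200) = 65/265 = 24.5%
- Arm B: 200/265 = 75.5%

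Both match the chances that Section 6.2.1 says subjects will be told. The test comes before randomisation, so these are also the expected shares of test reactions among randomised subjects.

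**3. Expected number of events**

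The protocol gives no first-use reaction rate for this product. Section 1.2.1 reports, for another THP over one month, that the most common product-related events each occurred in 0.4% to 1.3% of 237 subjects. That is about 1 to 3 subjects (0.004 × 237 = 0.9; 0.013 × 237 = 3.1). These are rates per type of event, so the rate for any reaction could be higher. The 5% row below is an assumption with no source in the protocol. All rows assume that all 265 randomised subjects try the THP, although the test is optional.

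Formulas: expected events = arm size × rate r; chance of at least one in Arm A = 1 − (1 − r)^65.

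| Rate r | Arm A: 65 × r | Arm B: 200 × r | Chance of at least one in Arm A |
| --- | --- | --- | --- |
| 0.4% | 0.26 | 0.8 | 23% |
| 1.3% | 0.85 | 2.6 | 57% |
| 5% (assumed) | 3.25 | 10 | 96% |

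Events in subjects withdrawn after the test are additional. The protocol gives no figure from which to estimate them.

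**The case against.** The strongest case against is that assigning adverse events to periods and adding a column for non-randomised subjects is ordinary SAP content, and the SAP is not at hand. Section 9.4 is one general sentence and does not forbid an extra column. The events are not hidden either: onset time and relationship are recorded, and the subject listings cover the whole safety population, including subjects withdrawn after the test. Exposure is at most two optional sticks.

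Much of this stands and keeps the point small. It does not remove it, because the protocol does more than stay silent. It sets a safety population that includes subjects without an arm and a summary that sorts everyone by arm, and the two do not fit together. Listings preserve an event but do not correct the table that misplaces it. Causality coding does not correct it either. Relationship is judged against the study product, and the only one listed is the THP, so an Arm A event could be recorded as product-related and still stand under cigarettes.

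Three stronger readings are tempting, and the documents do not support them:

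- **That THP loses its first-use reactions altogether.** About 75.5% of randomised subjects go to Arm B, and Section 9.4 keeps their test reactions in the THP column.
- **That the A-to-B comparison is tilted by the test events.** The test precedes randomisation, so the expected rate of test reactions is the same in both arms. The fault lies in what the Arm A events are attributed to, and in the missing column for withdrawals.
- **That Arm B is selected for tolerance of the THP.** Subjects leave before randomisation, so both arms are selected alike. This limits generalisability but does not bias the randomised contrast.

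**Conclusion.** The point holds as a cheap improvement with small expected impact. Under the protocol's own rules, product-test adverse events in subjects later randomised to Arm A (24.5% of those randomised) are summarised under conventional cigarettes. Those in subjects withdrawn after the test appear in no by-arm summary.

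For Arm A the expected size is about 0.3 to 0.9 events per type of event at the rates quoted for another THP, and about 3 if 5% of first users react. Both figures assume that every randomised subject takes the test. The number lost through post-test withdrawal cannot be estimated from the protocol. If the SAP already separates the product-test period, Section 9.4 only needs to be brought into line with it.

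**What to change.** In Section 9.4, summarise adverse events with onset from the first test stick until the start of randomised product use in a separate column or table labelled THP product test.

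- The denominator is everyone who used at least one stick, including enrolled-not-randomised subjects.
- Leave these events out of the on-study columns for both Arm A and Arm B.
- Report how many subjects withdrew after the test and how many of them had an adverse event.

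The safety population definition needs no change, because the Day 1 safety assessments already bring these subjects in.

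The cost is one extra table and recording the clock time of the product test; onset time of adverse events is already collected. The THP safety summary may look slightly less favourable.

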1. STUDY PROCEDURES
   1. Specific Restrictions/Requirements
      1. Concomitant Medication

Subjects should avoid medication that interferes with the cyclooxygenase pathway (anti‑inflammatory drugs such as aspirin and ibuprofen) from 14 days prior to Visit 1 until Check-out at Visit 13.

Subjects should also not use any drugs or substances (except tobacco) known to be strong inducers or inhibitors of CYP enzymes (formerly known as cytochrome P450 enzymes) within 14 days or 5 half-lives of the drug (whichever is longer) prior to each clinic visit. A list of such drugs and substances known to modulate CYP enzymes can be found at the following location: http://medicine.iupui.edu/clinpharm/ddis/main-table/. If additional clarification is required, the Investigator or their appropriately qualified designee will contact the Medical Monitor.

During the study, subjects will be instructed not to take any medication, including over‑the‑counter products, without first consulting with the Investigator. The Investigator will contact the Medical Monitor for questions regarding episodic use. Proton pump inhibitors, antidepressants, hypnotics, and benzodiazepines are allowed. Antibiotics are allowed for episodic use, provided that they are not strong inhibitors or inducers of CYP enzymes (eg. ciprofloxacin, clarithromycin, erythromycin.). If a subject is taking a concomitant medication not listed in the protocol at Screening, eligibility should be discussed with the Medical Monitor before enrolling the subject.

If any medication is required, the name, strength, frequency of dosing and reason for its use will be documented in the subject's eCRF by the Investigator or their appropriately qualified designee on the appropriate page of the eCRF.

Herbal medications, vitamins, and supplements should be avoided for 3 days prior to each clinic visit, unless agreed as acceptable by the Investigator and/or Medical Monitor (details provided in Section 8.4).

- - 1. Smoking and Nicotine Use

Subjects will be asked to provide a urine sample for a cotinine screen at Screening and Visit 1 to ensure that they are currently using nicotine-delivering products (Arms A, B, and D) or that they are non-smokers and do not otherwise use nicotine-delivering products (Arm E). Subjects will also be asked to provide an exhaled breath CO test at Screening to confirm whether they have smoked conventional cigarettes. Subjects in Arms A, B, and D will only be enrolled into the study if their urine cotinine level is greater than 200 ng/mL and their exhaled breath CO level is ≥ 7 ppm. Subjects may be rescreened to confirm CO levels are ≥ 7 ppm if they have a low CO level at Screening.

- - 1. Diet

Subjects will fast for at least 6 hours prior to each study visit at which clinical laboratory evaluations will be performed. Subjects should also refrain from large meals, and caffeine‑containing food (eg, chocolate) and drinks for at least 4 hours before the AIx measurements, and all food and drink for 1 hour before NO measurements. Spirometry will also be conducted at least 2 hours after eating. At site visits, subjects may be offered a light meal following completion of fasted assessments.

Subjects will be advised to refrain from consuming barbequed or chargrilled food for 48 hours prior to Check-in for each study visit.

Subjects will be advised that they must not eat food containing poppy seeds for 3 days before both Screening and Check-in for each visit, as consumption of poppy seeds can lead to a positive opiate result in the drugs of abuse screen.

- - 1. Alcohol

Subjects will be instructed to refrain from consuming alcohol for 24 hours prior to clinic visits.

Subjects will be instructed not to consume on average more than 28 units of alcohol per week if male or 21 units of alcohol per week if female for the duration of the study.

- - 1. Exercise

Subjects will be requested not to undertake vigorous exercise outside of their usual routine from 7 days before clinic visits. Subjects will not undertake vigorous exercise (including the 6-minute walk test) within 30 minutes prior to spirometry assessments.

- - 1. Blood Donation

Subjects must not donate blood during the study or for 12 weeks (male) or 16 weeks (female) after the safety Follow-up Visit.

- - 1. Contraception

Female subjects participating in the study who are of non-childbearing potential will not be required to use contraception. Women of non-childbearing potential are defined as permanently sterile (i.e. due to hysterectomy, bilateral salpingectomy, bilateral oophorectomy, or confirmed tubal occlusion) or postmenopausal (defined as at least 12 months post-cessation of menses without an alternative medical cause). Postmenopausal status will be confirmed with a screening serum follicle-stimulating hormone (FSH) level greater than 40 mIU/mL.

Female subjects of childbearing potential must be willing to use a highly effective method of birth control (i.e. contraceptive measure with a failure rate of < 1% per year) in conjunction with male barrier contraception (i.e. male condom with spermicide) from Check-in at Visit 1 until the end of the Follow-up Visit. Highly effective methods of contraception include:

- Intrauterine device (IUD; e.g. Mirena®). Steel or copper IUDs are acceptable.
- Established use of oral, implantable, injectable, or transdermal methods of contraception associated with inhibition of ovulation.
- Male sterilization (performed at least 90 days prior to Screening), with verbal confirmation of surgical success. For female subjects on the study, the vasectomised male partner should be the sole partner for that subject.
- Bilateral tubal ligation (performed at least 90 days prior to Screening).

Male subjects will be surgically sterile for at least 90 days, or when sexually active with female partners of childbearing potential will be required to use a male condom with spermicide from Check-in to Visit 1 until after the Follow-up Visit. Sexual intercourse with female partners who are pregnant or breastfeeding should be avoided unless condoms are used from Check-in at Visit 1 until the end of the Follow-up Visit. Male subjects are required to refrain from donation of sperm from Check-in at Visit 1 until the end of the Follow-up Visit.

Subjects who practice true abstinence, because of the subject’s lifestyle choice (i.e. the subject should not become abstinent just for the purpose of study participation), are exempt from contraceptive requirements. Periodic abstinence (e.g. calendar, ovulation, symptothermal, post-ovulation methods) and withdrawal are not acceptable methods of contraception. If a subject who is abstinent at the time of signing the ICF becomes sexually active they must agree to use contraception as described above and as outlined in the ICF.

For subjects who are exclusively in same sex relationships, contraceptive requirements do not apply. If a subject who is in a same sex relationship at the time of signing the ICF becomes engaged in a heterosexual relationship, they must agree to use contraception as described above and as outlined in the ICF.

- 1. Clinical Assessments

The timings of all measurements to be performed during the study may be subject to change based on the ongoing review of the safety and tolerability results.

- - 1. Demographic Data

Socio-demographic data (sex, age, race, and ethnicity) will be recorded at the Screening Visit.

- - 1. Smoking History and Willingness to Quit Smoking

Subjects will be asked about their smoking history at Screening. This will include questions to: evaluate whether the subject has smoked for at least the last 5 consecutive years, determine the number of cigarettes smoked by the subject per day on average, check that the subject has smoked their chosen brand of conventional cigarette consistently for at least 6 months, and to determine if the subject regularly uses any nicotine or tobacco product other than commercially manufactured filter cigarettes and/or roll your own cigarettes. In addition, the subject will be asked if he/she is planning to quit smoking within the next 12 months. A colour photocopy or photograph of each subject’s usual cigarette pack, including surface showing product details, will be taken.

- - 1. Medical History and Concomitant Diseases

Relevant medical history, as determined by the Investigator or their appropriately qualified designee, will be documented at Screening and Check-in at Visit 1. Medical history will include any clinically significant neurological, gastrointestinal, renal, hepatic, cardiovascular, psychiatric, respiratory, metabolic, endocrine, haematological or other major disorders. Medical history is defined as any condition that started and ended prior to Screening. A concomitant disease is any disease that started prior to and which was still ongoing at Screening.

- - 1. Vital Signs

Supine blood pressure, supine pulse rate, respiratory rate and axillary body temperature will be measured at the times indicated in the Schedule of Assessments (Appendix 15.1). Vital signs will also be performed at other times if judged to be clinically appropriate.

Blood pressure and pulse rate will be measured using automated monitors. Subjects must be supine for at least 5 minutes before blood pressure and pulse rate measurements.

Respiratory rate will be measured as per the standard institutional practice.

Axillary body temperature will be measured singly using a digital thermometer.

- - 1. Physical Examination

A full physical examination will be performed at Screening, and a symptom driven physical examination will be performed at the times indicated in the Schedule of Assessments (Appendix 15.1).

- - 1. Height, Body Weight, and BMI

Height in meters (to the nearest cm), and weight in kilograms (to the nearest 0.1 kilogram) in underclothing and without shoes will be measured at Screening.

The BMI at Screening will be calculated using the following formula:

BMI = body weight (kg)
 [height (m)]^2^

- - 1. Electrocardiography

A single 12‑lead resting ECG will be recorded after the subject has been supine for at least 5 minutes at the times indicated in the Schedule of Assessments (Appendix 15.1). The 12‑lead ECG will be repeated once if either of the following criteria applies:

- The QT interval corrected for heart rate using Fridericia’s method (QTcF) is >500 msec
- The QTcF change from the baseline (pre-product use) is >60 msec

If repeated, the repeat values will be used for data analysis.

Additional 12‑lead ECGs will be performed at other times if judged to be clinically appropriate or if the ongoing review of the data suggests a more detailed assessment of ECGs is required.

A physician will perform a clinical assessment of each 12-lead ECG. Clinical site reference ranges will be applied to all ECG parameters determined throughout the study.

The ECG machine will compute the PR and QT intervals, QTcF, QRS duration and heart rate.

- - 1. Lung Function Tests

Spirometry pre and post short-acting bronchodilator will be conducted, as indicated in the Schedule of Assessments (Appendix 15.1). At Screening, post‑bronchodilator spirometry (salbutamol; 4 x 100 µg, administered using a spacer) will be conducted 15 minutes (± 5 minutes) after completion (last attempt) of pre‑bronchodilator spirometry. At Screening, spirometry will be conducted at least 1 hour after smoking, at least 2 hours after eating, and at least 30 minutes after any vigorous exercise.

Spirometry will be used to measure:

- Peak flow
- FVC
- Forced expiratory flow 25‑75% (FEF 25-75%)
- FEV_1_

Spirometry testing will be performed in accordance with procedures of the American Thoracic Society/European Respiratory Society.^21^ Spirometry predicted values will be standardized to the Global Lungs Initiative predictive set.^22^

Measurements will be repeated if there are technical issues during testing or if the subject shows signs of fatigue. Measurements will not be repeated if the results fall under the levels required for enrolment in the study (Section 5.4). If a subject shows signs of fatigue during repeated testing, testing will be halted to ensure that the subject does not become exhausted and will only be recommenced at the physician’s discretion. No more than 8 manoeuvers should be performed. The spirometry traces will be copied and inserted into the source documents. The spirometer must be kept calibrated as recommended by the manufacturer.

- - 1. Clinical Laboratory Evaluations

Blood and urine samples will be collected for clinical laboratory evaluations at the times indicated in the Schedule of Assessments (Appendix 15.1). Subjects will fast for at least 6 hours prior to blood collection for clinical laboratory evaluations. Subjects may drink water during this fasting period.

Additional clinical laboratory evaluations will be performed at other times if judged to be clinically appropriate or if the ongoing review of the data suggests a more detailed assessment of clinical laboratory evaluations is required.

The Investigator or their appropriately qualified designee will perform a clinical assessment of all clinical laboratory data.

Blood samples will be taken for the clinical laboratory panel. Details of all blood samples collected in this study are presented in Section 7.4.2.The following evaluations will be performed:

| **Serum biochemistry:** | **Units** | **Haematology:** | **Units** |
| --- | --- | --- | --- |
| Aspartate aminotransferase (AST) | IU/L | Haemoglobin | g/dL |
| Alanine aminotransferase (ALT) | IU/L | Haematocrit (packed cell volume [PCV]) | % |
| Alkaline phosphatase | IU/L | Total and differential leukocyte count | 10^9^/L & % |
| Gamma‑glutamyl transferase (GGT) | IU/L | Red blood cell (RBC) count | 10^12^/L |
| Sodium | mmol/L | Platelet count | 10^9^/L |
| Potassium | mmol/L | Mean cell volume (MCV) | fL |
| Chloride | mmol/L | Mean cell haemoglobin (MCH) | pg |
| Calcium | mmol/L | MCH concentration (MCHC) | g/dL |
| Inorganic phosphate | mmol/L | **Urinalysis:** | **Units** |
| Glucose | mmol/L | Microscopic examination | + |
| Urea | mmol/L | pH | NA |
| Uric acid | µmol/L | Specific gravity | NA |
| Total bilirubin | μmol/L | Protein | + |
| Direct bilirubin | μmol/L | Glucose | + |
| Creatinine | μmol/L | Ketones | + |
| Total protein | g/L | Bilirubin | + |
| Albumin | g/L | Blood | + |
| Total cholesterol | mmol/L | Nitrite | neg/pos |
| Triglycerides | mmol/L | Urobilinogen | + |
| Creatinine phosphokinase (CPK) | IU/L | Leukocytes | cells/field |
| Blood urea nitrogen (BUN) | mmol/L | Urine pregnancy test^d^ | neg/pos |
| **Serology^a^:** | **Units** | Urine drug screen^e^ | neg/pos |
| Hepatitis B surface antigen (HBsAg) | neg/pos | **Additional Tests** |  |
| Hepatitis C antibody | neg/pos | Alcohol breath test | neg/pos |
| Human immunodeficiency virus (HIV)^b^ | neg/pos |  |  |
| **Hormone Panel^c^:** | **Units** |  |  |
| Follicle‑stimulating hormone (FSH) | mIU/L |  |  |
| Human chorionic gonadotropin (hCG; serum pregnancy test) | IU/L |  |  |

^a^ Screening only
^b^ HIV1/2 and p24 antigen
^c^ In all females at Screening only
^d^ Female subjects only. A positive urine pregnancy test will be confirmed with a serum pregnancy test. See Schedule of Assessments in Appendix 15.1 for scheduled timepoints.
^e^ Urine drugs of abuse screen will be conducted for amphetamines, barbiturates, benzodiazepines, cocaine, ecstasy, methamphetamine, morphine, methadone, tricyclic antidepressants, and tetrahydrocannabinol.
neg = negative
pos = positive

- - 1. Urine Drugs of Abuse Screen and Alcohol Breath Test

Subjects will be asked to provide urine samples for drugs of abuse screens at the times indicated in the Schedule of Assessments (Appendix 15.1). Urine samples will be screened for the presence of the following drugs of abuse: amphetamines, barbiturates, benzodiazepines, cocaine, ecstasy, methamphetamine, morphine, methadone, tricyclic antidepressants, and tetrahydrocannabinol.

Subjects will be screened for the presence of breath alcohol at the times indicated in the Schedule of Assessments (Appendix 15.1).

- - 1. Body Fat Analysis

Subjects’ body fat will be measured at the times indicated in the Schedule of Assessments (Appendix 15.1) using an OMRON BF511 machine according to the manufacturer’s instructions. The following parameters will be calculated:

- Body fat (%)
- Visceral Fat (up to 30 levels)
- BMI
- Skeletal Muscle (in %)

Body fat measurements will be taken at least 2 hours after meals.

- 1. Sample Collection for Biomarker and Exploratory Endpoint Assessments
     1. Exhaled Carbon Monoxide and Nitric Oxide

Exhaled carbon monoxide (CO) will be measured using the EC50 Micro III Smokerlizer (Bedfont) CO meter, or similar device. Exhaled NO will be measured using an Aerocrine NIOX VERO device. Subjects will not be allowed to use any study products/smoke any cigarettes or eat within 30 minutes prior to CO or NO level measurements. Subjects should also avoid all food and drink for 1 hour prior to NO measurements. Levels will be measured at the times indicated in the Schedule of Assessments (Appendix 15.1).

- - 1. Urinary BoE and BoBE

Spot urine samples will be used for the urine drugs of abuse screen, cotinine test, urine pregnancy test, and safety urinalysis.

Pooled 24-hour urine samples will be collected for analysis of urinary BoE and BoBE. Creatinine in urine will also be calculated and used to report BoBE as amount per unit of creatinine.

Samples will be transported and stored as detailed in Section 7.4.

- - 1. Blood Sampling for BoE, BoBE, and Exploratory Endpoints

Blood samples will be collected as described in the laboratory manual. Samples will be transported and stored as detailed in Section 7.4.

- 1. Sample Handling, Transport and Storage

All samples (urine and blood) will be transported on dry ice for analysis, with replicate samples being shipped independently.

- - 1. Urine Samples

For BoE and BoBE analyses, urine samples will be collected over concurrent 24-hour time periods beginning on the day before each study visit. All urine voided during the 24‑hour period will be collected and samples aliquoted for the various analyses. The samples will be refrigerated at between 2°C to 8°C. Additional sample handling instructions will be provided in the laboratory manual.

The urine samples collected during a single 24-hour interval will be pooled together and weighed. The samples will be related to the day on which the 24-hour collection period ended. The pooled samples will be thoroughly mixed before providing aliquots for analyses. The total volume of all urine collected over each 24-hour period will be calculated from weight and specific gravity. Urine aliquots will be stored in suitably labelled tubes at the temperatures indicated in the laboratory manual pending assay.

- - 1. Blood Samples

Blood samples will be collected by qualified and trained site personnel. The following blood volumes will be withdrawn for each subject:

|  | **Volume per Blood Sample (mL)** | **Maximum Number of Samples** | **Total Amount of Blood (mL)** |
| --- | --- | --- | --- |
| Serum biochemistry and hematology^1^ | 7.5 | 7 | 52.5 |
| Serology | 3.5 | 1 | 3.5 |
| White blood cell count | 2.0 | 14 | 28.0 |
| s-ICAM1 | 4.0 | 10 | 40.0 |
| HDL and LDL | 2.0 | 14 | 28.0 |
| Cholesterol and triglycerides^2^ | 1.0 | 4 | 4.0 |
| CEVal (Hb adduct) | 10.0 | 7 | 70 |
| Other BoBE | 5.0 | 10 | 50.0 |
| Serum NMR lipoprotein and metabolomics, and plasma BH2/BH4 ratio | 18.0 | 6 | 108 |
| Transcriptomics (WBC) | 5.0 | 4 | 20.0 |
|  | | **Total:** | **404** |

Abbreviations: BH2/BH4 = dihydrobiopterin/tetrahydrobiopterin; BoBE = biomarker of biological effect; CEVal = N-(2-cyanoethyl)valine; Hb = haemoglobin; HDL = high-density lipoprotein; LDL = low-density lipoprotein; NMR = nuclear magnetic resonance; s‑ICAM1 = soluble intracellular adhesion molecule-1; WBC = white blood cell.
Blood samples will be destroyed as per the laboratory’s standard procedures.
^1^ Glucose, total cholesterol, and triglycerides will be measured as part of serum biochemistry assessments. Serum biochemistry tests include follicle-stimulating hormone and serum pregnancy tests.
^2^ Samples will be collected specifically for cholesterol and triglyceride assessment at Visits 2 and 3.

